## Abstract

**Background:**

Despite the extensive use of antibiotics and the growing challenge of antimicrobial resistance, there has been a lack of substantial initiatives aimed at diminishing the prevalence of infections in nursing homes and enhancing the detection of urinary tract infections (UTIs).

**Objective:**

This study aims to systematize and enhance efforts to prevent health care–associated infections, mainly UTIs and reduce antibiotic inappropriateness by implementing a multifaceted intervention targeting health care professionals in nursing homes.

**Methods:**

A before-and-after intervention study carried out in a minimum of 10 nursing homes in each of the 8 European participating countries (Denmark, Greece, Hungary, Lithuania, Poland, Slovakia, Slovenia, and Spain). A team of 4 professionals consisting of nurses, doctors, health care assistants, or health care helpers are actively involved in each nursing home. Over the initial 3-month period, professionals in each nursing home are registering information on UTIs as well as infection and prevention control measures by means of the Audit Project Odense method. The audit will be repeated after implementing a multifaceted intervention. The intervention will consist of feedback and discussion of the results from the first registration, training on the implementation of infection and prevention control techniques provided by experts, appropriateness of the diagnostic approach and antibiotic prescribing for UTIs, and provision of information materials on infection control and antimicrobial stewardship targeted to staff, residents, and relatives. We will compare the pre- and postintervention audit results using chi-square test for prescription appropriateness and Student *t* test for implemented hygiene elements.

**Results:**

A total of 109 nursing homes have participated in the pilot study and the first registration audit. The results of the first audit registration are expected to be published in autumn of 2024. The final results will be published by the end of 2025.

**Conclusions:**

This is a European Union–funded project aimed at contributing to the battle against antimicrobial resistance through improvement of the quality of management of common infections based on evidence-based interventions tailored to the nursing home setting and a diverse range of professionals. We expect the intervention to result in a significant increase in the number of hygiene activities implemented by health care providers and residents. Additionally, we anticipate a marked reduction in the number of inappropriately managed UTIs, as well as a substantial decrease in the overall incidence of infections following the intervention.

**International Registered Report Identifier (IRRID):**

DERR1-10.2196/60099

## Introduction

Life expectancy has been steadily increasing in the European Union. Population projections estimate that by 2050 the old-age dependency ratio, calculated as the number of individuals older than 65 years per 100 people of working age, will reach 50% [1]. The rise in the ageing population and the pressure on the health care provision systems across European countries has led to reductions in hospital beds and more patient care being provided in long-term care facilities [2]. In 2019, there were an estimated 2.9 million residents in such facilities, corresponding to approximately 0.7% of the total population in the European Union [3].

Residents in nursing homes are more prone to frequent and severe infections [4]. In general, infections are highly prevalent among older people, especially those living in nursing homes, as they are more vulnerable to urinary tract infections (UTIs), respiratory tract infections, and acute bacterial skin- and soft-tissue infections [5]. Although recent estimates are lacking, approximately 2 million infections occur in US nursing homes each year [6]. Residents in care homes are particularly susceptible to infections due to factors such as immunosenescence, multiple comorbidities, functional impairment, the use of indwelling devices such as catheters and feeding tubes, close living proximity, recent acute care admissions, and frequent contact with nursing staff and medical equipment [7-10]. Microorganisms can be found on residents, relatives, and friends, on surfaces in the facility, and even on the hands or gloves of health care professionals (HCP) and medical equipment. Without appropriate and adequate cleaning and disinfection methods, the germs may spread to other residents and the environment. In younger healthy individuals, the immune system fights off germs and prevents infection; however, the declining ability of the body and immune systems to resist germs makes older people more susceptible to infection and they can become infected more easily [11,12].

Antibiotic overprescribing for infectious diseases is high in nursing homes. In a recent project on the prevalence of antimicrobial agents in 3052 long-term care facilities in 24 European Union countries in 2016-2017, 4.9% of the residents had received at least 1 antimicrobial agent on the day of the survey [13]. This study also showed that for a 1% increase in the proportion of residents older than 85 years, the prevalence of antimicrobial use increased by 5%. In addition, approximately 30% of the antibiotics prescribed were given prophylactically, and most were given inappropriately, with a wide variation across European countries. Furthermore, the urinary tract was the most common body site for which antimicrobials are prescribed, with nearly 50% of the cases, and according to the authors, at least 60% of these antimicrobials prescribed for UTI were inappropriate, leading to a spread of multidrug-resistant uropathogens [13]. As a result, Watch and Reserve broad-spectrum antibiotics, as defined by the World Health Organization Access, Watch, Reserve classification [14], are commonly given to residents with these infections, perpetuating the problem of antimicrobial resistance (AMR), which is accompanied with higher morbidity, mortality, health, and intersectoral and societal costs [15].

In nursing homes, antibiotic prescribing decisions are known to be complex and influenced by many social and organizational factors [16-18]. Overdiagnosis of common infections largely explains antibiotic overuse for these infections. A review of 4 randomized controlled trials of interventions aimed at improving the diagnosis of UTIs in nursing home residents found that, despite being heterogeneous, the interventions used were to some extent successful, but there was no evidence that an intervention was feasible or sustainable following trial completion [19]. Several decision tools have been developed for the diagnosis of UTIs in nursing home residents to assist clinicians in identifying symptomatic UTI [20,21]. The overarching message is that there are no precise diagnostic rules for identifying UTI among elderly individuals in nursing homes. In general, there is agreement that nonspecific symptoms alone, such as changes in mental or functional status or changes in urine characteristics, including bad smell, color, or sediment, should not be used to diagnose UTI and that a diagnosis of UTI in nursing home residents should not be made on urinalysis or urine culture without UTI-specific symptoms.

Antibiotic-resistant bacteria have the potential to spread between individuals through direct or indirect contact. Therefore, the implementation of infection prevention and control (IPC) strategies plays a crucial role in reducing the risk of infection [22]. These strategies not only contribute to a decrease in the number of infections but also effectively and efficiently reduce antimicrobial consumption, thereby limiting opportunities for misuse [23]. It is essential to emphasize the significance of infection prevention, biosecurity measures, and control practices in managing all infectious microorganisms, as they minimize the reliance on antimicrobials and, consequently, hinder the development and spread of resistance [24]. Unfortunately, there is a general lack of IPC measures and antimicrobial stewardship (AMS) programs in nursing homes across Europe [13]. In addition, most countries exhibit weak interprofessional collaboration and inadequate integration of health and social care delivery, leading to increased mortality, as evidenced during the COVID-19 pandemic [25,26].

In summary, in the effort to urgently decelerate the development of AMR, there is a need for evidence-based nursing home-focused AMS policies and IPC strategies aimed at preventing and controlling the spread of infections, as well as promoting appropriate antibiotic use across health care settings. Our objective is to assess the impact of a multifaceted intervention aimed at nursing home HCPs on preventing common infections, particularly UTIs. Additionally, we aim to evaluate the effectiveness of this intervention in reducing the percentage of inappropriate antibiotic use for common infections. By targeting HCPs with comprehensive training and resources, we hope to improve infection control practices and promote more judicious use of antibiotics, ultimately enhancing the quality of care for nursing home residents.

## Methods

### Study Design

This is a before-and-after intervention study in HCPs working in nursing homes. We are using the Audit Project Odense methodology [27], as the strategy to implement the multifaceted actions suggested in point 4.2 of the European Union’s AMR Guidelines for long-term care facilities states [23]: “establish a multi-faceted approach which includes elements such as education of nursing and medical staff, audits of antimicrobial use, feedback to the prescribers, and targeting identified areas of antimicrobial overuse and misuse.” The improving antibiotic use in nursing homes by infection prevention and control and antibiotic stewardship (IMAGINE) project was initiated in January 2023 and is planned to finish in December 2025. The consortium includes 12 partners from 9 countries, as indicated in Table 1.

**Table 1 table1:** Partners in IMAGINE^a^.

Participant organization name	Abbreviation	Role
Institut Català de la Salut and Fundació Institut Universitari per a la Recerca a l'Atenció Primària de Salut Jordi Gol, Spain	ICS or IDIAP	Coordinator of the project. Spanish coordinator
The Capital Region of Denmark	CAP	Preparation of materials for intervention. Danish coordinator
Research Unit for General Practice Odense, Denmark	RUPO	Audit Project Odense methodology
Szeged Autumns Nursing Home, Hungary	SAN	Hungarian coordinator
University of Ljubliana, Slovenia	UOL	Slovenian coordinator
Medical University of Lodz, Poland	MUL	Polish coordinator
Slovak Medical University in Bratislava, Slovakia	SMU	Slovak coordinator
Ltd Mano Seimos Gydytojas (My Family Doctor)	FDC	Lithuanian coordinator
University of Crete, Greece	UOC	Greek coordinator
University of Las Palmas de Gran Canaria and Fundación Canaria Parque Científico Tecnológico	ULPGC or FCPCT	Analysis and evaluation of the results
Spanish Society for Family and Community Medicine	SEMFYC	Dissemination and training in communication skills
European Union of Geriatric Medicine Society	EUGMS	In charge of dissemination of results

^a^IMAGINE: improving antibiotic use in nursing homes by infection prevention and control and antibiotic stewardship.

### Aims

The primary objectives of this study (IMAGINE project) are aimed at increasing the IPC elements implemented by 50% and decreasing the incidence of inappropriate antibiotic consumption for UTIs by 40%, with a subsequent 20% reduction in the incidence of UTIs. Different secondary objectives are planned: (1) reduction in inappropriate use of urinary catheters in nursing home residents; (2) reduction in the percentage of inappropriate antibiotic use for the prophylaxis of UTIs; (3) reduction in the number of Watch and Reserve antibiotics from the World Health Organization Access, Watch, Reserve classification; (4) improvement in the satisfaction of nursing home HCPs, residents, and relatives; (5) reduction in the incidence of health care–associated infections treated with antibiotics others than UTI; and (6) reduction in the percentage of hospital admissions.

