### Data Analysis Plan

The data collected in the specific registration charts have a primary function at the individual level of health professionals, that is, helping them to improve their practice by reconsidering their treatment choices considering clinical evidence, guidelines, and professional consensus [31]. The second function is to analyze the data to evaluate the effect of the intervention. In each audit, data are recorded for all antibiotics prescribed during the 3-month period. We aim to record a minimum of 50 cases in each of the nursing homes recruited (at least 100 nursing homes), yielding an approximate number of 5000 cases in each registration period.

We will apply the chi-square test to determine the frequencies and appropriateness of prescriptions before and after the intervention and Student *t* test for the number of hygiene elements implemented in the nursing homes to test the null hypothesis of no effect of the interventions. To measure the potential reduction in UTIs, we will assume that antibiotics are always prescribed for these infections and every antibiotic is associated with a new episode of UTI [32]. The number of hygiene elements implemented will be compared with a threshold that will be defined during the participatory action research analysis. The appropriateness of antibiotic prescriptions will be defined according to an algorithm based on symptoms and patient characteristics that will be developed at the start of the project. We will also estimate the effect of the interventions on inappropriate prescriptions for UTIs using multilevel logistic regression models with 2 levels: cases and HCP participants, to allow for the fact that patients belonging to the same HCP are not independent of each other [33]. Statistical significance will be considered with *P*<.05. The data will be analyzed using the current version of the Stata statistical program (version 18, StataCorp LLC).

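### The 40% primary aim is set on the incidence of inappropriate UTI antibiotics, but the stated analyses estimate the share of prescriptions that are inappropriate, so their estimate cannot be read against the target

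*Protocol article*

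**What the plan says.** The Aims section gives numeric targets for the primary objectives. Two matter here: "decreasing the incidence of inappropriate antibiotic consumption for UTIs by 40" per cent, and "with a subsequent 20% reduction in the incidence of UTIs". Both are worded as incidences, and the Discussion likewise speaks of rates of inappropriate consumption.

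The Data Analysis Plan states: "We will apply the chi-square test to determine the frequencies and appropriateness of prescriptions before and after the intervention". The Abstract assigns the same test to prescription appropriateness. The plan adds a two-level logistic regression of inappropriate UTI prescriptions, with cases nested in health care professionals.

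To measure the fall in UTIs, "we will assume that antibiotics are always prescribed for these infections and every antibiotic is associated with a new episode of UTI". Data are recorded for all antibiotics prescribed in each audit, February to April 2024 and February to April 2025. No rate model or population denominator is named for the 40% aim.

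**The concern.** An incidence counts inappropriate courses over a population and a period. A share divides those courses by all UTI courses. The two give the same relative change only if the total number of UTI courses stays constant, and this protocol aims to reduce that total. The stated analyses would therefore produce a share, or an odds ratio, that answers a different question from the one the target asks.

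At stake is whether a numeric primary objective was met. If the observed fall in the share is set beside 40%, an intervention that reached its aim will appear to fall well short. The reverse can also happen: the share can drop because appropriate courses increase, with no change in the incidence of inappropriate ones. If the measure is left open until both audits are in hand, the choice could be influenced by the results.

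**Working it through.** **The plan's own figure.** 50 cases × 100 homes = 5000 cases per audit, which reproduces the stated approximate number. The article gives no power calculation to reproduce.

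**Inputs**
- Inappropriate UTI courses after the intervention: 1 − 0.40 = 0.60 of baseline (Aims).
- Total UTI courses after: 1 − 0.20 = 0.80 of baseline (Aims, with the one-antibiotic-one-episode rule in the Data Analysis Plan).
- Baseline share inappropriate, p: not a stated design assumption. The Introduction cites a survey in which "at least 60% of these antimicrobials prescribed for UTI were inappropriate". I take p = 0.60 as an assumption and vary it.

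**Case A: both aims met exactly.** New share = 0.6p / 0.8 = 0.75p, a 25% relative fall at any p. At p = 0.60 this is 36/80 = 45.0%.

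**Case B: inappropriate courses fall 40%, appropriate courses unchanged.** New share = 0.6p / (0.6p + 1 − p).

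| Baseline p | New share | Relative fall |
|---|---|---|
| 0.40 | 28.6% | 29% |
| 0.50 | 37.5% | 25% |
| 0.60 | 36/76 = 47.4% | 21% |
| 0.70 | 58.3% | 17% |

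At p = 0.60 total UTI courses fall by 24% (100 to 76), so this case slightly overshoots the 20% aim.

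**Limiting cases at p = 0.60**
- Total constant: 36/100 = 36%, the full 40% fall. This conflicts with the 20% UTI aim.
- All UTI courses down 40% alike: 36/(36 + 24) = 60%. The incidence aim is met and the share does not move.
- Appropriate courses unchanged and the share down 40% to 36%: x/(x + 40) = 0.36 gives x = 22.5, so inappropriate courses would have to fall by 62.5%.

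**The odds ratio.** Before adjustment it equals the ratio of inappropriate courses (after/before) divided by the same ratio for appropriate courses. It is 0.60 in case B, because appropriate courses do not change. In case A at p = 0.60, appropriate courses go from 40 to 80 − 36 = 44, and the odds ratio is 0.60/1.10 = 0.55. It therefore tracks the target only if appropriate prescribing is constant, which the logistic model cannot show.

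**Power.** Assume half of the 5000 cases are UTIs and ignore clustering. Power to detect 60% against 47.4% is then above 99.9%. Detecting some effect is not the difficulty.

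**The case against.** The strongest reply is that the plan tests only the null hypothesis of no effect. Nothing in it sets the share against 40%, and a move from 60% to about 47% would be detected easily. That stands. A reader might infer that a successful intervention would be declared a failure, and the documents do not support this. The problem lies in interpreting the size of the effect.

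A second reply is that the data already suffice. All antibiotics are recorded in two calendar-matched windows in the same participants, so counts of inappropriate courses follow directly. The word frequencies in "chi-square test to determine the frequencies and appropriateness of prescriptions before and after the intervention" may even point to a comparison of counts. It stands that the information is collected, and this makes the remedy cheap. It does not stand that the plan already uses it: a chi-square test on prescriptions, with no population or period as denominator, does not estimate an incidence, and the logistic model is explicitly on cases.

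A third reply concerns size. The 60% is background literature, stated as a minimum. A reader might infer that the share always falls by about half the target. That depends on p = 0.60 and on constant appropriate prescribing. The protocol's joint aims give 25%, or 62.5% of the target (25/40).

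Two further extensions should not be drawn. The Introduction's "reducing the percentage of inappropriate antibiotic use for common infections" concerns common infections in general, so it is not a restatement of the UTI aim. Secondary objectives such as "reduction in the number of Watch and Reserve antibiotics" lack a stated denominator, but an article commonly leaves that to a full protocol or analysis plan, which is not shown here.

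**Conclusion.** The mismatch is real and lies between two things the article itself states: an incidence target of −40%, and analyses conditional on a prescription. Meeting the 40% and 20% aims exactly would lower the share by 25%. This figure uses only the protocol's own targets and its one-antibiotic-one-episode rule. With appropriate courses unchanged the fall is 21% at an assumed 60% baseline, and 29% to 17% for baselines of 40% to 70%.

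The conclusion is limited to the measure of effect. The planned test of no effect remains usable, and the audits collect what is needed to compare counts. What the stated analyses do not give is an estimate that can be judged against the 40% objective.

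**What to change.** For the 40% aim, add a before/after rate ratio of inappropriate UTI courses. Use home-level counts over the two equal 3-month audits in a count model (Poisson or negative binomial) that allows for clustering by nursing home. Where homes can supply resident-days or occupancy, include it as an offset. Report the rate ratio with its 95% CI against 0.60, and give the share inappropriate alongside it. Apply the same count comparison to the 20% UTI aim, with 0.80 as the reference.

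The alternative is to keep the share as the measure and restate the target as a proportion, giving the assumed baseline and the assumed change in total UTI courses.

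Either choice should be written down before the second-audit data are analysed.

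The basic count ratio needs no new data; occupancy figures need a small retrieval effort. The main downside is that counts are more sensitive than the share to completeness of recording. Charts are filled in on paper by volunteers, and lower recording effort in the second audit would look like a fall in incidence. That is the reason to report both measures.

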### Data Collection

A specific registration chart has been developed considering the characteristics and the quality improvement areas identified during the preparatory study performed in 2023. During the audit period, the participants are using the Audit Project Odense registration chart developed to record all the antibiotic prescriptions made in the nursing home. At most, 10 main groups and a maximum of 45 variables are used to describe the topic being investigated [27]. The main groups are lined up in a logical way, for example, focus of infection, symptoms, indwelling urinary catheter, diagnostic tests, treatment, and referral or not. The variables are exhaustive (include all possibilities) and exclusive (no overlapping), and all are in the same logic plan. One line is filled in for each case. As a rule, only ticks are allowed (no writing). At least 1 tick per main group is needed. Figure 2 depicts the definitive template used by IMAGINE. A short instruction sheet (maximum 1 page) has been provided for all participants. The instruction sheet specifies the registration period, the inclusion and exclusion criteria for the cases and briefly explains the content of each main group. Information about where to return the completed charts was given. A local contact person from the national teams is available for questions from the participants [27]. A pilot test of the chart was performed between October 2023 and November 2023 with 3 to 5 nursing home HCPs per country to ensure that the content of the registration chart was easily understood and to confirm that enough cases are available.

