**Figure 2 figure2:**
[figure not shown]
Template used in the IMAGINE (improving antibiotic use in nursing homes by infection prevention and control and antibiotic stewardship) project for patients receiving antibiotics. Subject to subsequent changes that may arise during the pilot study.

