### Ethical Considerations

The study is conducted in accordance with the protocol, the Declaration of Helsinki, the principles of Good Clinical Practice, The General Data Protection Regulation (of the European Union) 2016/679 and the Human Research Act as well as other locally relevant regulations. Appropriate regulatory or ethical approval has been sought in each of the countries taking part in the study, and all study procedures started after gaining approval on the basis of the master protocol, translated where necessary to local language. In Spain, the coordinating country, the study protocol was approved by the Ethics Committee of Institut Universitari d’Investigació en Atenció Primària (IDIAP Jordi Gol), Institute of Research in Primary Health Care (23/080-P).

Nursing homes have been contacted by local coordinators that have explained the study and handed over the information, giving the nursing home time to read it and ask any questions. Informed consent was obtained from all participants. HCPs are participating voluntarily in this quality improvement project. No personnel data are collected from either HCPs or patients. A nursing home can withdraw from the project at any time without giving any explanation. The information gathered from the residents’ prescriptions are personally nonidentifiable data and we are collecting the minimum data set necessary for the study. Data are anonymized from the beginning, coded in the template with the code of the nursing home and a consecutive number for each antibiotic treatment. Individual patient consent is therefore not required.

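### The catheter and admission objectives concern residents, but the only case-level record described covers antibiotic-treated cases, a group the intervention is meant to shrink

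*Protocol article*

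**What the plan says.** Under Aims, secondary objective 1 is a "reduction in inappropriate use of urinary catheters in nursing home residents" and secondary objective 6 is a "reduction in the percentage of hospital admissions". The first names residents as its population. The second is called a percentage, but the article does not say of what.

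The case-level data come from the registration chart. Data Collection describes it as a "registration chart developed to record all the antibiotic prescriptions made in the nursing home", and the legend of Figure 2 says the template is for the "project for patients receiving antibiotics". On the unit of record, Data Collection says "One line is filled in for each case", and Ethical Considerations says data are "coded in the template with the code of the nursing home and a consecutive number for each antibiotic treatment". The variable groups given as examples are "focus of infection, symptoms, indwelling urinary catheter, diagnostic tests, treatment, and referral or not", so catheter and referral sit on the same line as the antibiotic.

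Project Methodology adds that each home also registers its infection prevention and control (IPC) measures at some time during the audit. The content of that record is not shown. The article describes no resident count, resident-days, admission log or record of suspected infections left untreated.

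**The concern.** A resident without an antibiotic has no line on the chart. The chart's population is therefore defined by prescribing, and prescribing is what the intervention is designed to change. If the intervention succeeds, the second audit will hold a different mix of cases from the first. The share with a catheter or a referral can then differ between audits even if nothing has changed for any resident.

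Two things are at stake. First, a change in either measure could not be read as a change among residents. Second, hospital admission is the listed outcome best placed to show whether treating fewer residents does harm, yet an admission of a resident who was never treated in the home would appear on no line. The Data Analysis Plan adds to this by assuming that every UTI receives an antibiotic. The Discussion lists several limitations but not this selection.

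**Working it through.** **Inputs from the article**
- Planned cases: 50 per home in at least 100 homes (Data Analysis Plan).
- Target: a 40% cut in inappropriate antibiotic use for UTI (Aims).
- Background, from a cited survey and not from this study: about 50% of antimicrobials are for the urinary tract, and at least 60% of those are inappropriate (Introduction).

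**Assumed inputs:** the admission and catheter risks below. The article gives none.

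**The plan's own figure:** 50 × 100 = 5000 cases per period, as stated. With the 109 enrolled homes it would be 50 × 109 = 5450.

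**Lines lost if the target is met**
- UTI courses: 5000 × 0.50 = 2500
- Inappropriate UTI courses: 2500 × 0.60 = 1500
- Removed: 1500 × 0.40 = 600
- All-case denominator: 5000 → 4400. UTI denominator: 2500 → 1900.

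**Effect on a chart percentage.** Let r be the risk in inappropriate UTI courses and k the risk in all other courses, both held constant between audits. K is the number of other courses: 3500 over all cases, 1000 over UTI cases.
- Before = (K·k + 1500·r) / (K + 1500)
- After = (K·k + 900·r) / (K + 900)

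Admission with k = 10%, r = 2%:
- All cases: (350 + 30)/5000 = 7.6% → (350 + 18)/4400 = 8.4%, relative +10%. The count falls from 380 to 368.
- UTI cases: (100 + 30)/2500 = 5.2% → (100 + 18)/1900 = 6.2%, relative +19%. The count falls from 130 to 118.

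Other assumptions:

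| Measure | k | r | All cases | UTI cases |
|---|---|---|---|---|
| Admission | 10% | 0% | 7.0% → 8.0% | 4.0% → 5.3% |
| Admission | 10% | 5% | 8.5% → 9.0% | 7.0% → 7.6% |
| Admission | 10% | 10% | no change | no change |
| Admission | 10% | 15% | 11.5% → 11.0% | 13.0% → 12.4% |
| Any catheter | 25% | 10% | 20.5% → 21.9% | 16.0% → 17.9% |
| Any catheter | 20% | 20% | no change | no change |
| Any catheter | 10% | 20% | 13.0% → 12.0% | 16.0% → 14.7% |

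The catheter rows show any catheter. The article gives nothing from which inappropriate use could be modelled.

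**Chance of a significant result from case mix alone.** A two-sided chi-square test at 0.05, ignoring clustering, would flag the 10% v 2% admission shift about 28% of the time (all cases) or 30% (UTI cases). For the 25% v 10% catheter shift the figures are about 40% and 38%.

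**Admissions not seen.** If 2% to 10% of the 600 episodes no longer treated led to admission, with no antibiotic given in the home, 600 × 0.02 = 12 to 600 × 0.10 = 60 admissions would be on no chart line.

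**The case against.** The strongest reply is that the article never says objectives 1 and 6 will be measured from the chart. The variable groups are introduced as examples, and neither the template in Figure 2 nor the IPC record is shown. The article also does not describe every instrument: staff and resident satisfaction (objective 4) cannot come from an antibiotic chart. This stands in part. A reader might infer that both objectives will certainly be answered with a selection artefact, and the text does not prove that. It shows that the only case-level source described has this property, and that neither denominator is stated.

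A reader might also infer that the removed courses are the milder ones, so that both measures would worsen. The article does not say so. The Introduction and Discussion link overdiagnosis to non-specific signs such as confusion, falls and functional change, and such residents need not be at lower risk of admission or less often catheterised. The shift can go either way, or be nil.

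Three narrower points also stand:
- Only objective 6 is called a percentage. A catheter percentage is inferred from the chart. Referral is taken as the visible source for admissions but is not the same thing.
- The larger shifts (+19% admission, +12% catheter) apply to UTI cases only. Over all antibiotic cases, which Data Collection says are recorded, they are about +10% and +7%.
- It would be too strong to say that residents whose antibiotic is withheld never enter the data. One who is treated later in the home during the audit does enter. Those missed are never treated there, or are treated only in hospital.

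The reply does not remove the mismatch between objectives about residents and a sample selected by treatment. No later analysis plan can recover residents who were not recorded.

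**Conclusion.** The point holds as a mismatch between objective and data source. On the chart as described, a before-after comparison of catheter use or admission among antibiotic-treated cases is not a comparison among residents, and neither a rise nor a fall could be interpreted.

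The loss of about 600 of 5000 lines rests on the article's target and on survey figures that may not match these homes. The size and direction of any shift rest wholly on assumed risks: from about +10% to +19% relative for admission at 10% v 2%, through nil, to a fall of about 4% to 5% relative at 10% v 15%. These are secondary objectives, and the article sets no numerical target for them. The correction is still worth making, because it decides what may be concluded about residents and whether the admission outcome can serve as a check on harm.

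**What to change.** 1. State the denominator of objectives 1 and 6.
2. On the home-level IPC record already completed in each audit, add aggregate counts: residents (or mean occupancy, which gives resident-days), residents with an indwelling catheter on the registration day, how many of these lack an indication on the project's list, and all hospital admissions in the 3 months.
3. Take the 2024 admission and resident counts from administrative records where these exist.
4. Analyse per resident or per 1000 resident-days, with home as the cluster.
5. Where the 2024 baseline cannot be recovered, which is likely for catheter indication, limit the objective to antibiotic-treated cases. Report counts beside percentages, claim no reduction among residents, and list the selection as a limitation.

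**Cost.** Steps 1 and 5 need only wording. Steps 2 and 3 need a few aggregate figures per home and no personal data. The first audit is complete in all 109 homes, so the 2024 baseline would be retrospective and may be incomplete. The availability of administrative records in all 8 countries is an assumption, and using them adds a data source that may need to be cleared under the existing approvals.
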